### Sample size

The estimated sample size for the study is *n*=504 participants and is based on power calculations with the NCSS programme PASS 2019 [37]. Expecting a drop-out of 30% within the study period, we assume that data of *n*=352 subjects (*n*=176 per group) will be available at the end of the study. Both groups are planned to consist of 22 clusters, each providing *n*=8 participants on average. Thus, we will be able to show a significant difference between the mean numbers of unmet needs in both groups of at least one standard deviation with a power of 80%. In this set of assumptions, the intra-class correlation is set to 0.1. The coefficient of variation of cluster sizes (COV) is 0.63, which allows variance in cluster sizes between 8 and 37. The hypothesis is tested with a one-sided test at a significance level of *α*=0.05.

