Consenting GPs and specialists aid in the recruitment of participants in the trial. Information about the study will be available in participating GP offices and memory clinics and interested participants will be given a participant information sheet and a consent form. Participating practices will be cluster randomised into either the intervention or control group. Participants in memory clinics will be randomised individually or will be allocated to the group of their GP practice, if that practice is already part of the trial. In both cases, the allocation to the intervention and control group will be approximately 1:1. The allocation of GP practices to intervention and wait-list control group will be computer-generated with a random number generator. Participants will then be allocated based on their GPs’ group. If the participant’s GP is not yet part of the trial, the participant will be randomised individually and the GP practice (including all following participants naming this GP) will then be allocated to this group. For participants who name a GP who is not yet randomised as part of the GAIN trial, allocation concealment will be ensured as the randomisation code will be released when the patient has been recruited into the trial, which takes place after the baseline assessment has been completed. Since this is a trial involving care management, no blinding will take place. Participating centres, participants and researchers will be aware of group allocations.

Informed consent and agreement forms will be obtained. Participating physicians will sign an agreement form and participants will sign an informed consent form. Participants will be informed that their participation is entirely voluntary and that they are free to withdraw at any time; in the event of their withdrawal, any data collected up until that point would be kept by the research team. Participants’ consent forms will be collected in paper form either by the study nurses or the respective practice staff and send to the study centre via post. As part of the consent, participants will be asked to release from confidentiality of their patient data to allow trial relevant access to this information. This includes consent allowing patient and trial relevant communication between participants’ GPs and trial staff. This trial does not involve biological specimens.

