### Statistical analysis

The primary between-group comparisons will be based on analysing participants as initially randomised without imputation of missing data. A full analysis plan will be developed prior to completion of data collection and discussed and consented among all research partners.

Descriptive statistics of demographic and clinical data at baseline will be used to examine differences between both groups. The primary statistical analysis will be intention-to-treat (ITT) including all individuals providing baseline and follow-up values of the outcome variables. ‘As randomised’ analyses will be performed, considering outcome data obtained from all participants regardless of protocol adherence.

To investigate whether drop-out after the baseline assessment may be systematic and influences the results, we will run multivariable logistic regressions with drop-out (yes/no) as dichotomous outcome. The study group, sociodemographic variables, and clinical parameters based on the screening will be included as predictors. These analyses will be performed three times for (1) drop-out overall, (2) drop-out due to death and (3) drop-out due to withdrawal of informed consent.

To describe the study sample, appropriate summary statistics such as the mean, standard deviation, median, minimum and maximum for continuous variables and frequencies and percentages for categorical data will be used. The primary analyses will be conducted by using separate generalised linear models to test intervention effectiveness. The main outcome variables at the primary follow-up (6 months post-randomisation) will be the dependent variables. The model specification will correspond to the scale level of the outcome variable under investigation: number of unmet needs and health-related quality of life. The models will be adjusted for age, sex and living situation of the participants. The study group is the predictor of interest (usual care vs. intervention). The baseline value of the primary outcomes will be included as a covariate to reduce residual variance and to account for inter-individual variance at baseline. A positive intervention effect is defined as a significant regression coefficient (one-sided test) of the study group variable. To improve the quality of the regression models, possible interaction effects will be analysed for study group, age group, living situation and clinical parameters as sensitivity analyses.

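### The primary models, as written, make no allowance for clustering by GP practice, although practices are randomised and the sample size assumes an intra-class correlation of 0.1

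*Protocol article*

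**What the plan says.** On allocation, the protocol article (Study procedure) states: "Participating practices will be cluster randomised into either the intervention or control group". A memory-clinic participant takes the arm of their GP practice if that practice is already in the trial. Otherwise the participant is randomised individually, and the named practice, with everyone who later names it, follows into that arm.

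The Sample size section plans for clustering. "Both groups are planned to consist of 22 clusters", with 8 participants each on average and a coefficient of variation of cluster sizes of 0.63, and "the intra-class correlation is set to 0.1".

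The Statistical analysis section sets the primary model: "The primary analyses will be conducted by using separate generalised linear models to test intervention effectiveness". On covariates it says: "The models will be adjusted for age, sex and living situation of the participants". It adds the baseline value of the outcome, justified by variation between individuals. Success is defined there: "A positive intervention effect is defined as a significant regression coefficient (one-sided test) of the study group variable". The level comes from Sample size: "The hypothesis is tested with a one-sided test at a significance level of" 0.05.

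The article names no method for practice-level clustering in the analysis. It announces a full analysis plan, to be written before data collection ends, but does not say that this plan will add such a method.

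**The concern.** Caregivers allocated through the same practice share an arm and a GP. In the intervention arm the GP receives the needs feedback and decides which recommendations enter the care plan, so outcomes within a practice can be expected to correlate. The planning ICC of 0.1 says as much.

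A generalised linear model with the listed terms and its usual model-based variance treats about 352 analysed caregivers as independent. The between-practice component is then missing from the variance of the group coefficient. P-values are too small and intervals too narrow, and the error favours declaring the programme effective. It bears on both primary outcomes. The sample size calculation, which does allow for clustering, would also describe a different analysis from the one performed.

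**Working it through.** **Inputs, all from Sample size:** 22 clusters per arm; mean analysed cluster size m = 8; ICC = 0.1; coefficient of variation of cluster sizes CV = 0.63; one-sided α = 0.05; drop-out 30%.

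**Step 1. The plan's own figures.**
- Analysed number: 22 × 8 = 176 per arm, 352 in total. This agrees with the text.
- Enrolled number: 352 / 0.70 = 502.9, so 503. The stated 504 agrees within rounding (504 × 0.70 = 352.8).
- Stated power: "significant difference between the mean numbers of unmet needs in both groups of at least one standard deviation with a power of 80" per cent. This does not reproduce (step 5). It is a separate matter and is used here only to judge what the fix costs.

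**Step 2. Design effect.**

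DE = 1 + ((1 + CV²) × m − 1) × ICC

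1 + CV² = 1 + 0.3969 = 1.3969; 1.3969 × 8 − 1 = 10.175; DE = 1 + 10.175 × 0.1 = 2.02.

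The true standard error is √2.0175 = 1.42 times the one computed under independence, so the reported one is 1 − 1/1.42 ≈ 30% too small.

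**Step 3. Actual size of the nominal one-sided 5% test.**

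Size = 1 − Φ(1.645 / √DE)

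| ICC | CV | DE | √DE | Actual size | Simulated size |
|---|---|---|---|---|---|
| 0.10 | 0.63 | 2.02 | 1.42 | 12.3% | 12.2% |
| 0.05 | 0.63 | 1.51 | 1.23 | 9.0% | 8.9% |
| 0.02 | 0.63 | 1.20 | 1.10 | 6.7% | 6.9% |
| 0.10 | 0 (equal clusters) | 1.70 | 1.30 | 10.4% | 10.3% |

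The ICC values of 0.05 and 0.02 are assumptions, included to show the range. The simulation used 44 clusters, gamma-distributed sizes in the rows with CV 0.63, a normal outcome without covariates, and 20,000 runs under the null for each row.

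At ICC 0.1 a nominal 95% interval covers 2Φ(1.96 / 1.42) − 1 ≈ 83%.

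**Step 4. Single-participant clusters.** The article does not say how many memory-clinic entrants will be the only participant of their practice. Suppose, as an assumption, that 30% of participants are, with the rest clustered as planned. Then DE ≈ 0.7 × 2.0175 + 0.3 × 1 = 1.71 and the size is about 10.4% at ICC 0.1. At ICC 0.05, DE ≈ 0.7 × 1.5088 + 0.3 = 1.36 and the size is about 7.9%.

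**Step 5. After accounting for the cluster.** In the same simulation with unequal clusters, a test on weighted cluster means with 42 degrees of freedom, using the true ICC in the weights, rejected in 4.7% to 5.1% of runs for ICC 0.02 to 0.1.

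For power at ICC 0.1, the effective number per arm is 176 / 2.0175 = 87.2 and the standard error is √(2 / 87.2) = 0.151 SD. For a difference of 1 SD, power = Φ(1 / 0.151 − 1.645), which is above 99.9%; a noncentral t with 42 degrees of freedom agrees. The difference detectable with 80% power is (1.645 + 0.842) × 0.151 ≈ 0.38 SD.

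**The case against.** The best defence is that this is a condensed article with a full analysis plan still to come. GEE or a cluster-robust variance can be attached to a generalised linear model with exactly these covariates, and authors who plan with an ICC and a coefficient of variation evidently know about clustering. A reader might infer that the trial has decided to treat caregivers as independent. The text does not say that; it is silent on the variance. What does not stand is the step from there to calling this mere detail left to the plan. The article names the model class, lists the terms, defines success on one coefficient and does not call any of it provisional. Followed as written, it contradicts the article's own randomisation and sample size.

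A second objection concerns size, and it stands. A reader might take 12% as the error rate of both primary tests. That figure needs the planning ICC of 0.1 to be true, to persist after adjustment for baseline value and covariates, and to apply in clusters averaging 8. The ICC is also stated within a calculation for unmet needs only.

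Two wider readings are not supported. Recruitment route (practice or memory clinic) is not in the model, but both routes aim at about 1:1 allocation, and nothing shows that leaving it out biases the estimate or inflates the error. Clustering in the cost-effectiveness analysis concerns methods that the article leaves open, so its absence there is not a fault of this document.

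**Conclusion.** The point holds as a mismatch between the analysis as written and the design. If the model is run as described, with no cluster adjustment added by the full plan, the one-sided 5% test for unmet needs has an actual size of about 12% at the planned ICC of 0.1, and about 7% to 12% over ICC 0.02 to 0.1. These figures assume a mean cluster size of 8 and CV 0.63, and fall if many practices contribute a single memory-clinic entrant. For EQ-5D-5L the direction is the same for any positive ICC, but the size cannot be given because no ICC is stated. The figures are per outcome. The existence of the gap is certain from the text; its magnitude depends on the residual ICC.

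**What to change.** State in the Statistical analysis section, and carry into the full plan, that both primary models account for the GP practice that determined each participant's allocation. For memory-clinic entrants this is the practice of the named GP. Either a random intercept for practice, or GEE or cluster-robust variance with a small-sample correction, is acceptable. The correction matters because there are only 44 planned clusters. Name the chosen method for each outcome before the data are analysed.

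The cost is a change of wording and standard software. Intervals widen, by a factor of about 1.42 at the planned ICC. No participants need to be added for the stated unmet-needs difference of 1 SD, for which power with 176 per arm remains above 99.9%. The article reports recruitment still under way and the full plan still to be written, so the change can be prespecified.

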## Methods

### Trial objectives

The primary objective is to examine the effectiveness of a digitally supported care management programme to reduce unmet needs and improve quality of life in caregivers for PwD between a group receiving the intervention and a wait-list group receiving usual care. The secondary objectives are to assess cost-effectiveness of the programme and to examine whether the care management programme is associated with improvements in participants’ perceived burden, social support and use of services and resources.

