### Outcomes

The primary objective is to determine the effectiveness of a digitally supported care management programme to reduce unmet needs and improve health-related quality of life in caregivers for PwD in the primary care setting.

Primary outcomes are (a) number of unmet needs and (b) health-related quality of life. They are measured as follows:
The number of unmet needs will be assessed with a standardised assessment which is part of the tablet PC-based CMS and addresses the participants’ medical needs, home care needs, psychosocial needs and needs connected to the caregiver role. This needs assessment includes the Camberwell Assessment of Need for the Elderly (CANE) [26, 27].Health-related quality of life will be assessed using the EQ-5D-5L [28, 29]. This instrument comprises five dimensions, namely, mobility, self-care, usual activities, pain/discomfort and anxiety/depression. Each dimension has five levels varying from no problems to extreme problems. Each level corresponds to a 1-digit number that expresses the level selected for that dimension ranging from 1 to 5 with higher numbers indicating more severe problems. The digits for the five dimensions can be combined into a 5-digit number that describes the participant’s health status.

Secondary outcomes of this trial are the following: (a) caregiver burden, (b) social support, (c) use of medical and non-medical services and (d) the use of resources in dementia. They are measured as follows:

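### The success rule does not say whether one or both primary outcomes must be significant; if either suffices at one-sided 0.05, the familywise error is up to 9.75%

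*Protocol article*

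**What the plan says.** Four places in the Protocol article bear on this.

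- **Trial objectives.** The primary objective concerns the "effectiveness of a digitally supported care management programme to reduce unmet needs and improve quality of life in caregivers for PwD". The two aims are joined by a plain conjunction.
- **Outcomes.** "Primary outcomes are (a) number of unmet needs and (b) health-related quality of life". Neither is ranked above the other.
- **Sample size.** The calculation covers unmet needs only: a difference between the "mean numbers of unmet needs in both groups of at least one standard deviation with a power of 80"%. The section adds: "The hypothesis is tested with a one-sided test at a significance level of" 0.05. This is the only place where a significance level is given.
- **Statistical analysis.** "The primary analyses will be conducted by using separate generalised linear models to test intervention effectiveness". The decision rule follows: "A positive intervention effect is defined as a significant regression coefficient (one-sided test) of the study group variable". No level is repeated here. The section also announces a later document: "A full analysis plan will be developed prior to completion of data collection and discussed and consented among all research partners".

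**The concern.** A definition of success should let a reader tell, from the two test results, whether the trial is positive. This one does so only when both tests agree. If one coefficient is significant and the other is not, the text does not settle the matter. The wording speaks of a single coefficient and comes straight after the statement that each outcome has its own model, so the natural reading is that either is enough.

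Under that reading the trial has two chances to succeed by luck, each at the full level, and its overall error rate exceeds the nominal 5%. Allocation is open to the researchers (Study procedure), and the Discussion links evidence of effectiveness to implementation in routine primary care. Which outcome may carry the claim should therefore not be left to interpretation once results are visible.

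**Working it through.** **Inputs**

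- Two primary outcomes, tested separately and one-sided (Outcomes; Statistical analysis).
- One-sided level 0.05 (Sample size, stated for unmet needs). Its use for the EQ-5D-5L is an assumption.
- Correlation r between the two test statistics: not given. Assumed, with 0 to 0.8 shown.
- 22 clusters per arm with 8 participants on average, ICC 0.1, coefficient of variation of cluster sizes 0.63, 30% drop-out (Sample size).

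**The plan's own figures**

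No familywise error rate is stated, so there is none to reproduce. The participant numbers agree: 2 × 22 × 8 = 352, and 352 / 0.7 = 503 against the stated 504.

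The stated power does not reproduce:

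- Design effect = 1 + ((0.63² + 1) × 8 − 1) × 0.1 = 2.018.
- Effective size per arm = 176 / 2.018 = 87.2.
- Power at 1 SD is above 99.99%.
- The difference detectable with 80% power = (1.645 + 0.842) × √(2 / 87.2) = 0.376 SD.

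That mismatch is a separate issue. It does not affect the error rates below, but it matters when the cost of a remedy is judged.

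**Familywise error, no true effect on either outcome**

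Either suffices: 1 − Φ₂(1.645, 1.645; r), where Φ₂ is the bivariate normal distribution function. For r = 0 this is 1 − 0.95² = 0.0975.

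Both required: 1 − 2 × 0.95 + Φ₂(1.645, 1.645; r).

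| r (assumed) | Either suffices | Both required |
|---|---|---|
| 0 | 9.75% | 0.25% |
| 0.3 | 9.29% | 0.71% |
| 0.5 | 8.78% | 1.22% |
| 0.8 | 7.52% | 2.48% |

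If only one of the two outcomes is truly unaffected, a both-required rule errs only when that outcome's test falsely rejects. Its error is therefore at most 5% in every case.

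**Fixed sequence, unmet needs first**

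If unmet needs are truly unaffected, any false claim requires a false rejection at the first step: at most 5%. If unmet needs are truly improved and quality of life is not, a false claim requires a false rejection at the second step: again at most 5%. The first test is the test already planned, so its power does not change.

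**Splitting alpha, for comparison**

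One-sided 0.025 for each outcome gives 1 − 0.975² = 4.94% if the tests are independent. The detectable difference rises to (1.960 + 0.842) × √(2 / 87.2) = 0.424 SD, and power at 0.376 SD falls from 80% to 70.1%.

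**The case against.** The strongest reply is that the article nowhere states an either-or rule. The objective joins the two outcomes with a conjunction, and if both must succeed there is no inflation. It stands that a reader may infer the either-or rule but cannot cite it as adopted. The both-required rule is no better documented: the objective is not a decision rule, and a trial that needs two successes would have to be powered for both, while this one is sized on unmet needs alone. The ambiguity remains.

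Second, the 0.05 level is printed only for the unmet-needs hypothesis. This also stands. Its use for the EQ-5D-5L is an assumption, although the article offers no other level.

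Third, testing order and alpha allocation are often left to the analysis plan, which is announced but not shown. A missing adjustment method would therefore not be a finding by itself. The point rests on the success definition that the article does state and that leaves the decision open.

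Fourth, 9.75% is the value for independent tests. Both outcomes come from the same caregivers, so a positive correlation is plausible and lowers the figure. Even at 0.8 it is 7.5%.

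Two further inferences are tempting. A reader might add an allowance for clustering, because the analysis section names no cluster term, and arrive at a much larger error. The section is silent on clustering and does not say it will be ignored. The ICC is given for the unmet-needs calculation only, and the matter is distinct from multiplicity. A reader might also conclude that one-sided 0.025 costs nothing because power at 1 SD remains above 99.9%. That relies on the 1 SD figure, which does not correspond to the stated 80%; at about 0.38 SD the cost is roughly ten percentage points.

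**Conclusion.** The point holds as a defect in a stated rule. With two primary outcomes in separate models, the definition of a positive effect does not say whether one or both must be significant, and it sets no order and no adjustment. If either suffices and one-sided 0.05 applies to both, the familywise one-sided error is up to 9.75%, and between 7.5% and 9.3% for assumed correlations from 0.8 down to 0.3. These figures assume a non-negative correlation; the upper limit for any correlation is 0.05 + 0.05 = 10%. If both are required, the error is at most 5%. The documents do not show that the trial has chosen the looser rule, only that their wording permits it.

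**What to change.** Amend the success definition in the Statistical analysis section, and carry it into the analysis plan before outcomes are compared by group. The number of unmet needs is tested first at the full stated one-sided alpha. The EQ-5D-5L is tested confirmatorily, at the same level, only if the first test is significant. Otherwise its estimate and confidence interval are reported without a confirmatory claim. Unmet needs go first because the trial is sized on that outcome. State the level explicitly for the EQ-5D-5L as well.

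The change takes one or two sentences, with no change to sample size or data collection. The real cost is that a quality-of-life benefit could not be claimed as confirmatory if unmet needs fail. If the sponsor wants each outcome able to stand alone, an alpha split would do it, at the loss of power shown above. If both outcomes were always meant to be required, saying so would also close the gap, but the power for that joint requirement would then have to be shown.
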